#### **Study Design, Setting, and Participants**

A randomized controlled trial is designed to compare the effect of the iExaminer teaching method with the traditional method for teaching the fundus examination. This study's participants will consist of 115 medical students in a general medicine clinical clerkship rotation from 2017 to 2018. The participants will be randomly assigned to either the teaching method group using the iExaminer system (intervention group) or the teaching method not using the iExaminer system (control group). As guidance, faculty advise students about their grip, posture, procedure, angle, and light intensity in each group. For the iExaminer teaching method, faculty teach fundus examination skills using the iExaminer system while sharing screens with students. On the other hand, in the traditional teaching method, faculty teach fundus examination skills while students describe what they are seeing. All instruction time will be standardized to 30 minutes. Three different teachers will be randomly assigned to each session. We create the instructional design and train the faculty to minimize the educational effects.

The participants examine the fundus on the retina simulator (EYE Examination Simulator®; Kyoto Kagaku Co, Kyoto, Japan) using PanOptic ophthalmoscope before and after the educational session (pre-test and post-test). All participants will have watched instructional videos on standard use of the PanOptic ophthalmoscope and will have been prepared for the interpretation of typical fundus findings before the pre-test. In the pre-test and post-test, the students will be assigned three cases using a retina simulator. They will observe one eye for 90 seconds in each case. For each case, they will respond to a multiple-choice question asking if the case was a normal fundus, optic disc edema, pathological optic disc cupping, or not observed. The diagnostic accuracy of funduscopy findings and time taken to identify funduscopy findings will be assessed in pre-test and post-test.

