### **Statistical Analysis**

Statistical analyses will be performed using SPSS Statistics for Windows 22.0 (IBM Corp. Armonk, NY), with the level of significance set at  $P < 0.05$ . Diagnostic accuracy in funduscopy findings and time taken to identify funduscopy findings will be compared between the groups by using the two-way analysis of variance (ANOVA). Assuming an  $\alpha$  error of 0.05,  $\beta$  error of 0.2, power of detection of 0.8, and effect size  $f$  of 0.25, a sample size of 128 tests (a total of 180 tests would be done in each group) will be required for each group to allow for comparison of the diagnostic accuracy of fundus examination.

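### The 128 tests that the protocol requires for each group are, at its own inputs, the total for both groups (64 per group)

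*Protocol*

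**What the plan says.** Section 4 (Method), Statistical Analysis, plans to compare diagnostic accuracy and time to identify the findings between the groups by two-way ANOVA at the 5% level. The factors are not named. The inputs are an alpha error of 0.05, a beta "error of 0.2, power of detection of 0.8, and effect size" f of 0.25. The result is that "a sample size of 128 tests (a total of 180 tests would be done in each group) will be required for each group".

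Study Design, Setting, and Participants gives the counts behind the second figure in that sentence. There are two randomised groups, and "This study's participants will consist of 115 medical students". In each of the pre-test and the post-test, "the students will be assigned three cases using a retina simulator". The 180 tests per group match 60 students × 3 cases at one time point.

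**The concern.** In a standard ANOVA power calculation, f together with alpha and power yields the number of observations over all cells of the design. The value 128 is the familiar total for a one-degree-of-freedom effect at f = 0.25, which equals a standardised difference of 0.5 between two equal groups. The protocol attaches this number to each group, so its inputs and its output do not belong together.

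This is the protocol's only calculated sample-size requirement, and it is the figure a reader would use to judge the planned size. As printed, it sets 128 against 180 per group, whereas the stated inputs set 64 against 180.

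**Working it through.** **Inputs.** From Statistical Analysis: alpha 0.05, power 0.80, f = 0.25. From Study Design: two groups. Assumed, because not stated: 1:1 allocation, and group and time (pre, post) as the two factors. Each effect then has one numerator degree of freedom. Tests are treated as independent, as the protocol's calculation does.

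**Formula.** Power = P(F′ > F crit), where F′ is noncentral F with df1 = 1, df2 = N − k and noncentrality λ = f² × N. N is the total over all k cells.

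**Step 1: find where 128 comes from.**
- N = 128 in total: λ = 0.0625 × 128 = 8. Power is 0.8015 with 2 cells and 0.8014 with 4 cells.
- N = 127 in total: power 0.798, just short of 0.80.
- The smallest sufficient total is 128 with 2, 4, 6 or 12 cells, so the choice of cells does not matter.
- Per group: 128 / 2 = 64.
- Hand check by normal approximation for d = 0.5: 2 × (1.960 + 0.842)² / 0.5² = 62.8, so 63 per group.

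The printed number is reproduced exactly as a study total.

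**Step 2: take the sentence as printed.** 128 per group is 256 in total, so λ = 0.0625 × 256 = 16.
- Power at f = 0.25 is 0.9786.
- The f with 80% power at N = 256 is 0.176 (power 0.801). As a check, 0.25 / √2 = 0.177.

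**Step 3: look for a choice that gives 128 per group (256 in total) at f = 0.25.**

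| Choice | Total N | Per group |
|---|---|---|
| df1 = 1, power 0.80 (as stated) | 128 | 64 |
| df1 = 2 | 158 | 79 |
| df1 = 3, four cells | 179 | about 90 |
| df1 = 5, six cells | 211 | about 106 |
| df1 = 1, power 0.90 | 171 | about 86 |
| df1 = 1, power 0.95 | 210 | 105 |
| df1 = 1, alpha 0.025 | 155 | about 78 |
| df1 = 1, alpha 0.01 | 191 | about 96 |

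Repeated-measures versions (2 groups × 2 times, correlation 0 to 0.75) need 18 to 112 subjects in total. None of these choices reaches 256.

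**Step 4: what each group means.** The same sentence says that "a total of 180 tests would be done in each group", which fits 60 × 3 for a randomised arm at one time point. The 128 therefore cannot be read as a count per cell, or as pre-test and post-test added together.

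**Step 5: compare with what is planned.** 180 per group exceeds both 64 and 128. Taking tests as independent at f = 0.25, power is 0.997 for 2 × 180 = 360 tests and 0.996 for 115 × 3 = 345 tests.

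**The case against.** **It changes nothing in the trial.** The error is on the safe side: no enrolment figure, test or decision rule depends on 128, and the planned tests exceed either version of the requirement. This stands, and it limits the weight of the point. It does not make the sentence right.

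**Other calculations come close to 128 per group.** There are two. A difference in pre-to-post change of 0.5 SD between groups is an interaction f of 0.125; it needs 505 independent tests over four cells, or 505 / 4 ≈ 126 per group per time point. A design effect of 2 for three tests per student, 1 + (3 − 1) × 0.5 with an intraclass correlation of 0.5, gives 128 × 2 = 256 in total. The first departs from the stated f of 0.25, and the second needs a correlation that the protocol never gives. Neither rescues the sentence. They do mean that a mislabelled total is the simplest explanation, not something the document states.

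**The target is clear.** A reader might infer that the effect or power the trial was sized for is now unknown. The protocol does not support that: f = 0.25 and power 0.8 are stated, and with them 128 is recovered exactly. The likely case is that both inputs are right and only the label is wrong.

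**The trial's planned size.** A reader might also infer that the whole plan is doubled. It is not: 115 students and 180 tests per group are separate planned counts and are untouched.

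**Conclusion.** The stated requirement is wrong by a factor of 2. At f = 0.25, alpha 0.05 and power 0.80, a one-degree-of-freedom effect in the two-way ANOVA needs 128 observations in total, 64 per group. As printed, 128 per group corresponds to power of about 0.98, or to f of about 0.18 at 80% power. This rests on equal allocation, an effect with df1 = 1 and independent tests.

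The error is conservative on the protocol's own unit and does not by itself leave the trial underpowered. A reader might conclude the opposite by setting 128 against the 115 students, where power would be about 0.76 if each student counted as one observation and f = 0.25 applied at that level. That conclusion does not follow from the mislabel. It depends on how strongly a student's three tests are correlated, for which the protocol gives no figure, and on the level at which f is defined. The choice of independent unit has to be settled separately.

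**What to change.** Replace the requirement in Statistical Analysis with: *a total of 128 independent observations (64 per group) is required for f = 0.25, alpha 0.05 and power 0.80.* If 128 per group was intended, keep it and state what produces it: f of about 0.18 at 80% power, power of about 0.98 at f = 0.25, or an explicit inflation factor with its source.

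The cost is one corrected sentence. Correcting the label changes neither enrolment, the number of tests nor the analysis. The correction should not be used to settle whether the student or the test is the independent unit, because that question could bear on enrolment.

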### **3. Selection of study subjects**

#### **a. Selection criteria**

This study's participants will consist of 115 medical students in a general medicine clinical clerkship rotation from September 2017 to July 2018. All data will be collected from those who have consented to the study. This program can be taken by all eligible students and can be taken with or without research consent.

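### The planned 180 tests per group does not follow from 115 students with three cases per occasion; it implies 120 students, although the stated requirement of 128 is still exceeded

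*Protocol*

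**What the plan says.** Protocol section 3.a states that the study's "participants will consist of 115 medical students in a general medicine clinical clerkship rotation from September 2017 to July 2018". The Study Design, Setting, and Participants part of section 4 repeats the 115 and describes random assignment to two groups without giving a ratio. The same part sets the number of tests per student: "In the pre-test and post-test, the students will be assigned three cases using a retina simulator".

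The Statistical Analysis part of section 4 takes the test, not the student, as the unit of sample size. With an alpha error of 0.05, power of 0.8 and effect size f of 0.25, it asks for 128 tests in each group. In parentheses it adds that "a total of 180 tests would be done in each group". It does not say whether the 180 counts one occasion or both.

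**The concern.** The 180 is the protocol's only comparison of what will be collected with what is required. A reader takes from it a margin of 180/128, about 41%. If 180 cannot be obtained from the stated students and cases, then either the student number or the test number is wrong, and the unit of the sample size is unclear. The 180 also counts raw tests, three from each student at each occasion, so the apparent margin is not in independent observations.

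**Working it through.** **Inputs.** From the protocol: 115 students; 3 cases per occasion; 2 occasions; f = 0.25; alpha 0.05; power 0.80; 128 tests required and 180 planned, both stated per group. Assumed: 1:1 allocation (57 and 58 students), because no ratio is given; and a range for the within-student correlation of tests (ICC), because none is given.

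**1. Trying to reproduce 180.**

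- One occasion: 57 × 3 = 171 and 58 × 3 = 174, average 172.5. The shortfall against 180 is 9/180 = 5.0% and 6/180 = 3.3%.
- Both occasions: 57 × 6 = 342 and 58 × 6 = 348, average 345, about 1.9 times 180.
- Without assuming a ratio: 180 in each group needs 360 tests per occasion, but 115 × 3 = 345. A 60/55 split gives 180 and 165. No split gives 180 in both groups.
- Backwards: 180/3 = 60 students per group, 120 in total. Over both occasions, 180/6 = 30 per group, 60 in total. Neither is 115.

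**2. Reproducing 128.** Power of the F test with one numerator degree of freedom uses non-centrality λ = f² × N, where N is the total over all cells. With f = 0.25 and N = 128, λ = 0.0625 × 128 = 8 and power is 0.801, with either two or four cells. At N = 127 it is 0.798. So 128 reproduces exactly as a total, that is 64 per group. Taken as 128 per group (N = 256), power would be 0.979.

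**3. What the gap in the count does to power, with tests treated as independent.** N = 360 (180 per group) gives 0.997. N = 345 (115 students, one occasion) gives 0.996.

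**4. Allowing for three tests per student at one occasion.** The design effect is 1 + (3 − 1) × ICC, and the effective total is 345 divided by it. Power is approximated by entering the effective total as N, with f kept on the scale of single tests.

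| Assumed ICC | Design effect | Effective tests per group | Effective total | Power |
|---|---|---|---|---|
| 0 | 1.0 | 172.5 | 345 | 0.996 |
| 0.1 | 1.2 | 143.8 | 287.5 | 0.988 |
| 0.2 | 1.4 | 123.2 | 246.4 | 0.974 |
| 0.3 | 1.6 | 107.8 | 215.6 | 0.955 |
| 0.5 | 2.0 | 86.3 | 172.5 | 0.904 |
| 1 | 3.0 | 57.5 | 115 | 0.757 |

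The effective number per group falls below 128 at ICC = (172.5/128 − 1)/2 = 0.17. It falls below 64, the number that corresponds to 80% power, only at ICC = (172.5/64 − 1)/2 = 0.85.

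The last row is also the power if f = 0.25 is defined on one score per student. On that definition, 120 students would give 0.775.

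**The case against.** The strongest reply is that 128 is the requirement and 180 only a remark in parentheses. On that view nothing required is missed: 171 to 174 per group is 34 to 36% above 128, and counting both occasions far exceeds even 180. This stands. A reader might infer from the mismatch that the required sample size is not delivered, and the protocol does not support that.

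A reader might also infer that clustering removes the margin, because the effective number per group drops below 128 at an ICC of about 0.17. That treats 128 per group as the threshold for 80% power, which it is not. At that ICC the effective total is 256 and power is still about 0.98.

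Nor does the figure of 76% show a shortfall caused by having 115 rather than 120 students. It needs either perfectly correlated tests or f redefined on student scores, and 120 students would then give 0.775, also below 0.80.

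Non-consent could lower the count, since section 3.a takes data only from consenting students. At an assumed 90% consent the count is 0.9 × 172.5, about 155 per group per occasion. But section 4 calls the 115 participants, so 115 may already be the consenting number, and 155 still exceeds 128.

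The reply does not remove the contradiction itself. Neither way of counting occasions, and no allocation ratio, turns 115 students into 180 tests in each group.

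**Conclusion.** The planned count is wrong as written. With 115 students and three cases, each occasion supplies 345 tests, or 171 to 174 per group at an assumed 1:1 allocation, against the stated 180. That is 3 to 5% short before any non-consent. That 345 is below the 360 needed is certain from the protocol's own figures; only the split by group rests on the assumed ratio.

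The effect is minor. The stated 128 per group is exceeded on either count, and with independent tests power changes by about 0.001. The larger numerical slip in the same sentence is the label on 128, which is the total for the stated inputs, assuming a comparison with one numerator degree of freedom. With the student as cluster, power stays at about 0.90 or more for assumed ICCs up to 0.5. It falls to 0.76 only at an ICC of 1 or if f is defined on student-level scores.

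**What to change.** Rewrite the sample-size sentence in the Statistical Analysis part of section 4 so that it:

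- gives 115 students (57 or 58 per group at 1:1) and 171 to 174 tests per group at each of pre-test and post-test, less any expected non-consent;
- says which occasion the sample size refers to;
- gives 128 as the total for f = 0.25, one numerator degree of freedom and 80% power, that is 64 per group;
- says whether f applies to single tests or to student scores, and quotes power for 115 students with the student as cluster over an assumed ICC range. With f on single tests this is about 0.99 at 0.1, 0.95 at 0.3, 0.90 at 0.5 and 0.76 at 1.

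If 120 students were meant, keep 180 as the count per group at each occasion and correct 115 in section 3.a and in the Study Design, Setting, and Participants part of section 4.

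The cost is one rewritten sentence. The stated margin becomes slightly less favourable, and no students need to be added.

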## **5. Study period**

- |                                    |                      |
|------------------------------------|----------------------|
| a. Sub Subject intervention period | 9/1/2017 – 8/31/2019 |
| b. Subject registration period     | 9/1/2017 – 7/31/2019 |
| c. Research period                 |                      |

## **6. Expected advantage and disadvantage of the study**

- a. Advantage  
The subjects will be trained to acquire fundus skills.

b. Disadvantage

In the control group, care should be taken so as not to cause any disadvantages by performing iExaminer teaching method after the end of the study.

**7. Informed consent**

This study was approved by the Ethics Committee of Chiba University School of Medicine (Chiba, Japan). A detailed explanation of the study was given to all participants, who confirmed that they fully understood the information before voluntarily giving informed consent to participate.

**8. Handling research in situations where there is an urgent and obvious crisis in the subject**

This research shall be conducted with the approval of the Chiba University Graduate School of Medicine Ethics Review Committee and the Chiba University Graduate School of Medicine Conflict of Interest Committee. Specifically, it will be enforced based on guidelines for clinical research, the Personal Information Protection Act, and guidelines for the proper handling of personal information in medical and nursing care-related businesses. In addition to the purpose and content of this study, the doctor in charge verbally states that the subject is free to cooperate in this study and that the subject will not suffer any disadvantages by not cooperating with the study. In addition, the questionnaires will be distributed and medical interviews will be conducted only for those who explained in writing and obtained consent.

**9. How to deal with health hazards**

Since this research targets information obtained within the scope of normal medical examinations, it does not perform any invasive behavior for direct research purposes. Therefore, there will be no disadvantage caused by this study.

**10. How to protect personal information**

Delete personally identifiable information and comply with anonymization. Although the survey form of the target person is used for data, it tries to protect personal information by anonymizing. The principal investigator is required to ensure the reliability of essential documents related to the implementation of research, etc. Documents or records etc.) shall be preserved and discarded 10 years after the publication of the research. All data is stored in a locker with a lock in the General Medical Department, Chiba University Hospital.

**11. Research funds and conflicts of interest**

There is no “possible conflict of interest” in the study planning, implementation, and reporting that will affect the outcome of the study and the interpretation of the results, and the conduct of the study will not harm the subject's rights or interests make sure.

## **12. Possible secondary use of samples and information and provision to other research institutions**

None.

## **16. Economic burden or reward for the research subjects**

There is no financial burden or reward for the subjects.

